**V. Study Procedures**

A. Recruitment Process:

1. ***Describe how you will identify, approach, and inform potential participants about your study. Include details about who will perform these activities and what their qualifications are.***

For all objectives, there will be no face-to-face or “in-person” interactions between study team members and research participants. We will work closely with in-country collaborators to obtain necessary national approvals for the study, including for the recruitment strategies outlined below.

For objectives 1, 2, and 4 the sampling of participants will be done using RDD. RDD is a method often used to select individuals to participate in a telephone survey through computer-facilitated random generation and dialing of digits that may comprise active telephone numbers. For objective 3, IVR surveys will be sent to a random sample of de-identified mobile phone numbers that were provided by a mobile network operator (MNO; i.e. a cell phone company or numbers list vendor) and/or which were collected from a previous household survey, where permission for re-contact was provided.

For all objectives, potential respondents will first receive a single SMS notification indicating that they will be sent a mobile phone survey shortly. The SMS will contain brief information on the survey’s purpose, the expected time commitment, and the survey’s sponsoring agency. An IVR survey will then be sent once to the same randomly generated mobile phone number where participants will be able to consent to the survey or refuse their participation (or CATI for microtrial #7). SMS notifications and IVR surveys will be sent by a mobile phone survey provider (e.g., VOTOmobile, a company that specializes in delivering IVR surveys and deploying RDD approaches globally) and who will be sub-contracted by investigators from JHU. For microtrials that contain a call center (*microtrials #5 and 7),* operators will be trained in human subjects research by the in-country partner. Training will include procedures on recruitment, consent, and interviewing techniques.

Once a respondent is contacted or participates in one of the proposed microtrial, they will be ineligible for participation in future microtrials. In each *microtrial*, there will be a single random selection of mobile phone numbers without replacement. However, since some participants own multiple mobile phones and phone numbers, it is possible that some participants may be randomly selected to participate in more than one microtrial.

*2.* ***Address any privacy issues associated with recruitment. If recruitment itself may put potential participants at risk (if study topic is sensitive, or study population may be stigmatized), explain how you will minimize these risks.***

Privacy issues associated with recruitment are anticipated to be minimal and similar to those associated with other face-to-face, phone or internet-based surveys. Participants will be sent an SMS alerting them of an upcoming survey and will then receive a phone call asking their willingness to respond to survey questions using their personal mobile phones. The incoming phone number will be the same for the text message and the phone call. Anyone not willing to complete the survey may choose to: 1) not answer the phone, 2) hang up any time after answering the phone, or 3) indicate their desire not to complete the survey by pressing a specified digit. Other individuals associated with or in proximity of respondents are unlikely to know that respondents are being recruited for the study unless the responded chooses to make this known.

B. Consent Process:

1. ***Describe the following details about obtaining informed consent from study participants. If a screening process precedes study enrollment, also describe the consent for screening.***

We are requesting a modification to written signed informed consent due to the nature of the research activities. Potential participants are unable to provide written informed consent as there is no face-to-face interaction. Moreover, as is common practice for brief IVR and CATI surveys, an abbreviated standardized verbal disclosure of key study information noting the voluntary nature of the survey will precede any data collection. After a brief introduction and opportunity for potential respondents to select their preferred language, potential participants will be read a brief description of the study and expected time burden in their language of choice. Potential participants will then be asked to “Press 1” if they would like to continue with the study. Individuals who do not “Press 1” will have the survey terminated. For participants in microtrial #5 and #7 where CATI surveys are conducted, the human operator will not proceed without a voluntary affirmative statement indicating the individual’s willingness to participate after he/she hears about the study.

*2.* ***Identify the countries where the research will take place, and the languages that will be used for the consent process.***

This study will be conducted in four of the following countries: Bangladesh, Lebanon, Kenya, Tanzania, Uganda, and Ghana. The consent/disclosure statement in the IVR survey will be made available in the most common languages for that study area. The statement will be translated into local languages and back-translated into English to ensure accuracy.

C. Study Implementation:

*1.* ***Describe the procedures that participants will undergo. If complex, insert a table below to help the reviewer navigate.***

**Study set-up**

Prior to enrollment and commencement of study, the NCD risk factor survey will be uploaded onto the web-based VOTOmobile IVR platform (See Appendix 1). VOTOmobile is a program that allows one to send audio recorded IVR surveys. The IVR surveys will be pre-tested prior to study commencement to identify and resolve any technical glitches, e.g. errors in skip patterns.

**Questionnaire**

A schematic of the mobile phone survey is found below. The MPS is comprised of several modular segments: (1) Language selection, (2) Introduction, (3) Demographic Screening, (4) Consent (5) NCD Modules and, (6) Incentive Delivery.

NCD modules are groups of questions on similar NCD behavioral risk factor topics covered in established NCD risk factor surveys such as WHO’s STEPS survey and the Global Adult Tobacco Survey (GATS). NCD modules include: tobacco use, alcohol consumption, dietary intake, physical activity, and current medications for blood pressure and diabetes.

To ensure that there will be an even distribution of answered NCD modules in those that do not complete the entire MPS, the order in which participants answer the NCD modules will be randomized, as illustrated in the figure below. For example, one participant may be presented NCD modules randomized in the following order: tobacco use, alcohol use, physical activity, dietary intake, and current medications for blood pressure and diabetes; while another participant may receive NCD modules in the order of physical activity, dietary intake, alcohol consumption, current medications for blood pressure and diabetes, and tobacco use. To preserve skip patterns programmed into the MPS, the order of questions within each module will not be randomized. The randomization of modules will occur in all *microtrials*. For the physical activity modules, participants will be randomized to receive one of two sets of physical activities questions: 1) International Physical Activity Questionnaires (IPAQ) or 2) Global Physical Activity Questionnaires (GPAQ).

**Figure 2. Components of the survey and randomization of NCD modules. The first several modular sequence will be fixed, and the NCD modules may be randomly ordered to prevent drop-off associated response bias.**

[figure not shown]

##

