This sample size is calculated based on the kappa statistic. With assumption of kappa= 0.75, a margin of error of 0.05%, an alpha of 0.05, and the proportion of positive responses=0.3, 405 participants who have completed the survey per study arm are needed. Adjusting for a 20% loss to follow-up from the first and second mobile phone survey and a 30% baseline completion percentage, 1688 participants who consented will be enrolled per arm and per country, for a total of 3376 participants across the two arms per country. With two arms and 4 countries, a total of 13,504 participants who provide consent across the four studies are needed.

Total Sample Size

For the baseline survey and seven microtrials, in each country, a total of 23,773 individuals who have consented to an MPS survey will be needed to fulfill a sample size of 6926 individuals who completed an MPS survey per country. As this protocol is being implemented in four countries, the overall sample size is 95,092 individuals who have consented to an MPS survey and 27,704 who completed a MPS survey

**Table 1.** Number of participants who consent to and complete a mobile phone survey per country

|  | **Col. A** | **Col. B** | **Col. C^*^**  [(Col B*100)/0.30] | **Col. D**  [Col A*Col B] | **Col. E**  [Col A*Col C] |
| --- | --- | --- | --- | --- | --- |
|  | # of study arms | N participants who completed survey per study arm | N participants who consented per study arm | Total N participants who completed survey | Total N participants who consented |
| **Objective 1** |  |  |  |  |  |
| *Baseline* | 1 | 100 | 334 | 100 | 334 |
| *Microtrial #1* | 3 | 376 | 1254 | 1128 | 3762 |
| *Microtrial #2* | 3 | 376 | 1254 | 1128 | 3762 |
| *Microtrial #3*** | 3 | 376 | 1254 | 1128 | 3762 |
| **Objective 2** |  |  |  |  |  |
| *Microtrial #4* | 4 | 376 | 1254 | 1504 | 5016 |
| *Microtrial #5* | 2 | 376 | 1254 | 752 | 2508 |
| **Objective 3** |  |  |  |  |  |
| *Microtrial #6* | 1 | 376 | 1254 | 376 | 1254 |
| **Objective 4** |  |  |  |  |  |
| *Microtrial #7* | 2 | 405 | 1688 | 810 | 3376 |
| **Total** |  |  |  | 6926 | 23,773 |

* For microtrial 7, we adjust for a 20% loss to follow-up from the first and second mobile phone survey.

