**Microtrial Designs**

A description of each of the seven *microtrials* and the baseline IVR survey follows. Differences between the *microtrial* design and the IVR questionnaire and delivery (sections detailed above) will be pointed out. A broad description of the *microtrials* can be found in Table 2. Where participants have the opportunity to earn an airtime incentive, participants will be told of the requirements to earn this incentive during the survey’s introduction.

Objective 1: Evaluation of Incentives

*Baseline IVR* Survey

The purpose of the baseline IVR survey is to assess baseline completion rates to inform sample size calculations for the seven *microtrials*, to finalize the questionnaire used in IVR delivery, and to ensure that the IVR platform is functioning well (i.e. delivering SMS notifications, IVR surveys, and incentives correctly and as indicated in the protocol). For the baseline IVR survey, a 30 question containing survey will be sent to randomly dialed participants at random times of the day (See Appendix 1 for the questionnaire to be used). An airtime-based incentive of approximately $1.00 USD will be transferred to a respondent’s mobile phone if the survey is completed (i.e. all questions answered). The exact amount of airtime incentive will be guided by the finding of the formative FGD (JHU IRB No: 0000709)

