This microtrial seeks to examine whether the survey’s modality (IVR versus CATI) has a differential effect on the survey’s response and completion rates and to assess the ‘inter-modal reliability’. Participants will be randomized to one of two arms: 1) IVR then CATI or 2) CATI then IVR. Participants in the first study arm will receive an IVR survey first, followed by a CATI survey 7 days later. Participants in the second study arm will receive a CATI survey first followed by an IVR survey 7 days later. At initial enrollment, participants will be clearly explained that they are being enrolled in a microtrial where they will be contacted twice. The questionnaires used in both study arms will the same. This crossover design will allow for an assessment of response consistency, adjusted for the risk of ‘priming’ after exposure to the prior modality. This is the only *microtrial* that has participants answer two NCD surveys. The amount/timing/structure of incentive will be guided by the first three *microtrials*; where the incentive that yielded the highest response and completion rates will be provided to all participants in *microtrial* #7.

Follow-up of Non-response, Refusals, and Incomplete Interviews

For participants who were selected for the seven *microtrials,* a random sub-sample of participants who did not initiate the IVR survey, refused to participate, or partially completed an IVR survey, will be called back by a human operator using the same telephone number that was associated with the IVR. The study team will attempt to reach individuals up to three times. Unreached follow-ups will be documented. If successfully reached, the team will consent and interview participants to explore reasons for participant’s non-response, refusal, or incomplete surveys using a semi-structured guide (See Appendix 2). Demographic information from non-responders, refusals, and incomplete surveys will also be collected and examined in relation to the distribution of those who fully complete the survey.

**Table 2.** Study designs for Microtrials

|  | **Microtrial#1**  **Incentive Amount** | **Microtrial#2**  **Incentive Timing** | **Microtrial#3**  **Incentive Structure** | **Microtrial#4**  **IVR Intro features** | **Microtrial#5**  **IVR vs Human Intro** | **Microtrial#6**  **Sampling frame** | **Microtrial#7**  **Survey Modality** |
| --- | --- | --- | --- | --- | --- | --- | --- |

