***4. Provide a brief data analysis* plan *and a description of variables to be derived.***

The contact rates, response rates, and completion rates will be tabulated for each of the microtrials by study arm; where contact, response, and completion rates are defined as:

The contact, response, and completion proportions^[[1]](#footnote-1)^ will be tabulated for each of the *microtrials* and by study arm where contact, response, and completion are defined as:

$$Contact Rate= \frac{CI+PI+R}{CI+PI+R+(NC+U)}$$

$$Response Rate= \frac{CI+PI}{CI+PI+R+NC}$$

$$Completion rate= \frac{\mathrm{CI}}{CI+PI+R}$$

**CI** (Complete Interview): a respondent that answered all applicable questions

**PI** (Partial interview): a respondent who consented to the survey but did not answer all questions

**R** (Refusal): a respondent who: 1) did not consent to the survey, or 2) formally withdrew during the survey

**NC** (Non-contact): a working phone number where the respondent picked up but did not engage with the survey. This is assessed by looking at the system log for time spent on the survey

**U** (Unknown): a phone number that cannot be determined whether it is a working phone number (the respondent did not pick up the phone) or not (the phone number is not eligible)

Respondents who report being less than 18 years old are considered ineligible. Ineligible respondents are excluded from the equations for contact, response, and completion rates.

Contact, response, and completion proportions will be compared by study arm for each microtrial and by incentive group. *A priori, a*n alpha of 0.05 will be used for hypothesis testing.

Partially completed surveys will be tabulated and stratified by both the question number, and the question content due to the randomization of NCD topic modules. Additionally, the average time spent answering, the number of “Don’t know” or “Refuse to answer” responses, and the number of times the question was repeated will be calculated for both the chronological question number and question content and stratified by study arm. For microtrial #7, test for agreement in survey responses between the survey modalities will be assessed using Cohen’s Kappa.

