In microtrial #7, participants will be asked to answer two surveys (IVR and call center [CATI]) composed of the same questions so that question validity can be assessed. For example, analyses will be conducted to observe whether some people may be more likely to report unhealthy habits when taking the automated IVR survey as compared to a call center because the human element is removed in an IVR survey.

Risk factor data will be collected and stored from other microtrials. This data will be compared to publically available results and national estimates to help determine if the protocol’s mobile-collected risk factor’s prevalence are similar to national estimates of household collected data. This will help answer whether the protocol’s mobile phone sample is as healthy, or unhealthy, as the traditionally administered surveys.

*5.*  ***Describe whether you are collecting or storing personal identifiers, and if yes, why you need them, and when and how you plan to dispose of them. Signatures on consent forms are considered to be identifiers.***

We will not collect personal identifiers via the consent process. Mobile phone numbers that were randomly generated are the personal identifiers. Because of the nature of the trial, the mobile phone numbers are needed to generate data. While phone numbers will initially be logged in the VOTOmobile platform alongside the data collected, immediately after each microtrial has been completed, the PI will download the database from the VOTOmobile platform and permanently delete the column containing mobile phone numbers. Phone numbers need not be retained for purposes of the study. No other potentially individually identifying data will be collected.

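### The random split between two physical-activity questionnaires stays in force in microtrial 7, so each physical-activity kappa rests on about half the planned pairs (about ±0.07, not ±0.05)

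*Protocol*

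**What the plan says.** Protocol section V.C.1, Questionnaire, describes random ordering of the NCD modules and states that "The randomization of modules will occur in all" microtrials. The next sentence adds that, for physical activity, "participants will be randomized to receive one of two sets of physical activities questions": IPAQ or GPAQ. No allocation ratio is given.

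The opening of Microtrial Designs says that departures from the general questionnaire and delivery will be flagged microtrial by microtrial. The microtrial 7 description flags none for this split. It describes an IVR survey and a CATI survey 7 days apart, in random order, and says "The questionnaires used in both study arms will the same". The data analysis plan (V.C, item 4) describes the two surveys as "composed of the same questions so that question validity can be assessed", and says that a "test for agreement in survey responses between the survey modalities will be assessed using Cohen’s Kappa".

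Section III.B, under Microtrial 7, sizes the study on kappa: "With assumption of kappa= 0.75, a margin of error of 0.05%, an alpha of 0.05, and the proportion of positive responses=0.3", concluding that "405 participants who have completed the survey per study arm are needed".

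**The concern.** Kappa needs the same item answered twice by the same person. IPAQ and GPAQ are two different sets of questions, so an IPAQ item has pairs only from people given IPAQ, and likewise for GPAQ. The sample size counts every completer as a usable pair for a generic item. For physical activity that is not so while the split applies.

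Physical inactivity is one of the four risk factors named in the Background, and microtrial 7 is the only place where agreement between modes can be estimated. A reader of the sample size section would expect ±0.05 for physical activity too, and the design as written does not deliver it. The second survey also runs on a different system (automated IVR against call-centre operators), and nothing states how the instrument given first is made known there.

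**Working it through.** **Inputs.** Kappa 0.75, proportion positive 0.3, alpha 0.05, 405 completers in each of two arms, 20% loss between surveys, 30% completion (all section III.B). The margin is printed as 0.05%; it is read here as 0.05 absolute, for the reason given in step 1. Assumptions not in the protocol: a 1:1 instrument split, and a binary item with equal margins in the two modes.

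**1. Reproduce the protocol's figure.** The large-sample variance of kappa per pair is

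V = (1−κ) × [(1−κ)(1−2κ) + κ(2−κ) / (2p(1−p))]

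V = 0.25 × [0.25 × (−0.5) + 0.9375 / 0.42] = 0.25 × [−0.125 + 2.2321] = 0.5268

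Pairs needed for a half-width of 0.05: N = 1.96² × 0.5268 / 0.05² = 809.5, so 810, or 405 in each of two arms. This matches the protocol. A one-sided alpha gives 570 in total, a margin of 0.10 gives 202, and a literal 0.05% gives about 8.1 million; none of these fits.

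Enrolment: 405 / 0.30 / 0.80 = 1687.5, so 1688 per arm, as stated. The ±0.05 therefore already uses every pair from both arms, with nothing in reserve for a split module.

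**2. Apply the split, with one instrument kept per person.** Pairs per instrument: 810 / 2 = 405. Half-width: 1.96 × √(0.5268 / 405) = 0.071, which is √2 = 1.41 times the planned margin.

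**3. Range over the assumed prevalence (κ = 0.75).**

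| Proportion positive | 810 pairs | 405 pairs |
|---|---|---|
| 0.2 | ±0.058 | ±0.082 |
| 0.3 | ±0.050 | ±0.071 |
| 0.5 | ±0.046 | ±0.064 |

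**4. Range over the unstated ratio.** A 2:1 split, as an example, gives 540 and 270 pairs: 1.96 × √(0.5268 / 540) = 0.061 and 1.96 × √(0.5268 / 270) = 0.087. Any unequal split makes one instrument worse than ±0.071.

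**5. What ±0.05 for each instrument would take.** 2 × 810 = 1620 pairs, or 810 per arm. 810 / 0.30 / 0.80 = 3375 consents per arm, so 6750 per country against the 3376 stated.

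**6. Conditional case.** Only if the instrument were drawn afresh at the second survey would 1:1 draws leave about 405 of the 810 pairs on different instruments and about 202 on each instrument twice, with 1.96 × √(0.5268 / 202.5) = 0.100.

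**The case against.** **The surveys are said to match.** A reader might infer from the missing carry-over rule that half the pairs will be mismatched and the margin will be ±0.10. The protocol does not support that. It randomises participants, not survey occasions; no re-draw is described; and the analysis plan says that both surveys carry the same questions. What stands is narrower: no sentence says how the first allocation reaches the second survey.

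**Scope.** The statement that module randomisation applies to all microtrials closes a paragraph about module order, and the IPAQ/GPAQ sentence follows it without repeating those words. That is fair. But the general questionnaire applies unless a microtrial flags a departure, and microtrial 7 flags none.

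**The ±0.05 belongs to a generic item, and 810 is not printed.** Both are true. The protocol promises no margin for physical activity in particular, and precision will vary by item. Yet only the pooled 810 reproduces 405 per arm. If the sponsor meant a separate kappa in each arm, 405 pairs already give ±0.071 for every module, and the split would bring physical activity to about 202 pairs and ±0.100 per arm and instrument. The split costs a factor of √2 either way.

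**Pooling.** A kappa stratified by instrument could use all pairs, and the statistical analysis plan, not shown, may define one. It would summarise agreement averaged over two instruments, not the reliability of either. Pooling four countries would give 1620 pairs per instrument and about ±0.035, but the sample size is set per country.

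**Usefulness and reach.** ±0.07 around 0.75 is still informative. Only one of five modules is affected, and the questionnaire may be shortened after the baseline survey. These points limit the weight of the concern but do not remove it.

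**Conclusion.** The concern holds in a limited form. The split applies in microtrial 7 on the protocol's own rule for exceptions, and the sample size makes no allowance for it. With one instrument kept per participant, each physical-activity kappa rests on about 405 pairs per country with a margin of about ±0.071 instead of ±0.05 (±0.064 to ±0.082 for prevalence 0.5 to 0.2). This rests on a 1:1 split, kappa 0.75, a binary item, and the margin read as 0.05 absolute. The other modules' kappas keep all 810 pairs, and contact, response and completion rates are untouched.

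The missing carry-over rule is a gap in specification, not evidence that pairs will mismatch. It should still be closed before fielding, because a mismatched pair cannot be repaired afterwards. Nor do the documents show any bias from drawing the module order separately for the two surveys, so no change to module order is asked for.

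**What to change.** 1. In the Questionnaire section and the microtrial 7 description, state that the physical-activity instrument assigned at a participant's first survey is used again at the second, whichever mode comes first. State the allocation ratio.
2. In section III.B, under Microtrial 7, state that per-instrument physical-activity kappas use about half the pairs, about 405 per country under 1:1, with a margin of about ±0.07.

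The cost is a few sentences and one programming rule. The two surveys must be linked by participant for any kappa, so the assignment can travel with that link. No extra participants are needed.

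**Option for the sponsor.** Giving every microtrial 7 participant the same instrument would restore 810 pairs and ±0.05. The price is real: all cross-mode reliability evidence on the other instrument is lost. Microtrials 1–6 cannot supply it, because each of their participants receives one survey and the NCD modules are delivered by IVR. Keeping both instruments at ±0.05 each would need about 6750 consents per country instead of 3376.
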